## Background

Urinary stone disease (syn. *urolithiasis*) is a widespread disease with tremendous impact on those affected and on societies around the globe. Nevertheless, clinical and health care research in this area seem to lag far behind cardiovascular diseases or cancer. This may be due to the lack of an immediate deadly threat from the disease and therefore less public and professional interest. There is a paucity of data on epidemiology and health care concerning urolithiasis in Germany and around the world. In Germany, Hesse et al. published the only available data on the incidence and prevalence of urinary stone disease in 2003 [1]. According to their data, the incidence and prevalence of urolithiasis are rising (incidence in 1979: 0.54%, 2001: 1.47%; prevalence 2001: 4.77%). This includes recurrent urolithiasis in 50% of patients within 5 years [2].

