### Risk factors

To date, little is known about sociodemographic and behavioral risk factors for recurrent urolithiasis [8]. Risk factors explaining recurrent stone formation in the vast majority of recurrent stone formers thus remain unaccounted for. However, evidence is pointing to specific characteristics that correlate with higher risks of recurrent stone forming: Men are more often affected than women (prevalence 5.5% vs. 4.0%) [1]. Fifty percent of patients are considered “high risk” patients with more than two stone-related events and/ or known risk factors for disease recurrence [9]. Risk factors for highly recurrent stone disease include general factors (early onset, family history of urolithiasis), specific stone compositions, diseases associated with stone formation (hyperparathyroidism, gastrointestinal disease, etc.), genetically determined diseases associated with stone formation (cystinuria, primary hyperoxaluria, etc.), and anatomical abnormalities of the urinary tract associated with stone formation [10]. Metabolic evaluations of recurrent stone formers may reveal abnormalities in urine chemistry associated with stone formation [2]. In addition, recent studies identified several gene mutations associated with nephrolithiasis [10].

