### Objectives

We will implement and assess the effectiveness of the RECUR registry for recurrent urolithiasis in the upper urinary tract as a distributed multi-institutional digital registry based on the technical infrastructure of the German Medical Informatics Initiative (MI-I).

Our purpose is to answer the following research questions:

Description of disease
burden: What impact does urolithiasis have on individual patients and the
health care system?Impact of the disease on
patient-reported outcomes (PROMs, e.g. working ability, perceived restrictions
of activity and participation due to urolithiasis, stone-related quality of
life) [19, 20]: trajectories of these outcomes will be analysedSocio-economic impact
(e.g., length of hospital stay, lost working days) [6, 21]: standardized unit
costs will be applied to quantify the costs of medical resource utilization;
analyses will be carried out from the healthcare perspectiveGender-dependent impact
of urolithiasis: subgroup analyses will reveal gender-specific aspects of the
disease burden [22, 23]Determination and
validation of risk factors: How can patients at risk of stone recurrence be
identified beyond the known risk factors?Personalized medicine:
taking into account individual variability in lifestyle and nutritional habits,
sociodemographic factors (age, education, socio-economic status), genes
[24–26]: multi-level models for change will be devisedDevelopment of a risk
score to predict the probability of stone recurrenceValidation of the risk
score using longitudinal registry dataDeduction of implications
for prevention and treatmentTreatment evaluation:
Which is the optimum treatment for individual patients? [27]Risk-adjusted comparison
of outcomes for different treatment options (e.g. surveillance vs. medical
treatment vs. surgical treatment): Propensity score matching analyses will be
conducted to compare outcomes; this method will help us estimate a given treatment’s
effect while accounting for the covariates that predict receiving the
treatment.We will focus on outcomes
relevant to patients such as disease recurrence, sick leave due to
urolithiasis, perceived restrictions of activity and participation due to urolithiasis.

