### Outcomes

Primary outcome variables of the registry are “stone recurrence” and “stone-related quality of life” using the German version of the Wisconsin Stone Quality of Life Questionnaire (WISQOL) [33]. Secondary outcomes include pain, functional restrictions, working ability, sick leave, and sequelae. Determining and confounding variables include individual and external risk factors.

Individual risk factors include clinical findings (size, weight, co-morbidity), laboratory results (including stone composition), radiology reports (including number, size and location of stones), medication, etc. (captured via DICs) and sociodemographic and lifestyle variables (nutrition, physical activity). Patients will be divided into risk groups to determine the effectiveness of different treatments. External risk factors include all interventions such as secondary prevention measures, non-surgical and surgical treatments for urolithiasis.

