### Data analysis

To answer research question 1 (description of disease burden), descriptive analysis methods will be used. The WISQOL will be analysed following the specifications of the developers [33]. No monitoring of PROMs during the study will take place. We will carry out an analysis of patterns of missing items and will take appropriate measures to deal with them.

Regarding research question 2 (determination and validation of risk factors), we expect missing data, that might occur not completely at random. Therefore, multiple imputations will be applied to reduce the chance of bias from missing data. Two-level multiple logistic regression models with the dependent variable stone recurrence will be conducted to account for cluster effects (patients are nested within centres). By using Receiver Operating Characteristics (ROC) analyses, we will determine the predictive power of the risk factors. The Youden Index and area under the curve (c statistic) will be calculated. As ROC curves do not consider time to event and right censoring, we will complement this analysis via survival analysis techniques like Kaplan–Meier or Cox regression analyses.

Since prognostic models derived from multivariable regression analysis lead to overestimated predictions when applied in new patients, we will internally validate our model with bootstrapping techniques. For external validation, it is essential to evaluate the performance of the model in a sample independent from those used to develop the model. This will be realized by comparing the prognostic capacity in the data set acquired in the first year with that in the second year.

For treatment evaluation (research question 3), propensity score matching will be applied. This method is increasingly used as an alternative to traditional regression to balance differences between treatment groups in descriptive and causal comparisons. To account for the nested data structure, propensity-score-weighted estimators for clustered data will be applied. Analyses corresponding to research question 1 will be conducted every six months, the other analyses annually.

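### The ROC measures fixed for research question 2 describe overall discrimination and do not show whether new factors improve prediction over the known ones

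*Protocol article*

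**What the plan says.** The Objectives section frames research question 2 as finding and validating risk factors and asks how patients at risk can be "identified beyond the known risk factors". Under the same question it lists the development and validation of a score for the probability of recurrence.

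The Risk factors section sets out what counts as known: early onset, family history, "specific stone compositions, diseases associated with stone formation", genetic disease and anatomical abnormalities. It says that sociodemographic and behavioural factors are poorly understood.

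The Outcomes section gives one predictor list: "Individual risk factors include clinical findings (size, weight, co-morbidity), laboratory results (including stone composition" and further clinical items, alongside nutrition, physical activity and sociodemographic variables.

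The Data analysis section then fixes the method. "Two-level multiple logistic regression models with the dependent variable stone recurrence will be conducted", with patients nested in centres and missing data multiply imputed. Next, "By using Receiver Operating Characteristics (ROC) analyses, we will determine the predictive power of the risk factors", and "The Youden Index and area under the curve (c statistic) will be calculated". Kaplan–Meier or Cox analyses are added because ROC curves ignore follow-up time and censoring. Validation is by bootstrap and by "comparing the prognostic capacity in the data set acquired in the first year with that in the second year".

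No section names a reference model of known factors, a difference in c statistic or any other measure of added prediction. The Machine learning section promises a statistical analysis plan, which is not at hand.

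**The concern.** To learn whether anything predicts recurrence beyond the known factors, the comparator has to be prediction from the known factors alone. The c statistic and the Youden Index carry no such comparator. Their built-in reference values are 0.5 and 0, which stand for no discrimination at all. A model that contains stone composition and co-morbidity can discriminate because of those two, whatever the lifestyle and sociodemographic items contribute.

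At stake is the part of research question 2 that is new. The registry collects app-based lifestyle and sociodemographic data partly to explain recurrence that the established factors leave unexplained. A single overall c statistic would leave open whether those items help to predict it.

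**Working it through.** The protocol states no sample size calculation, target c statistic or expected gain, so there is no figure to reproduce. The check has two parts.

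**Question against measure.** The question is about the change from known factors to known plus new factors. The measure is the level for the whole set. The planned safeguards act on that level:

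- The bootstrap removes optimism from the overall c statistic.
- The year-1/year-2 comparison asks whether the overall performance holds in later data.
- The Cox and Kaplan–Meier analyses deal with time and censoring.

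A score driven only by known factors can pass all three.

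**Simulation.** Inputs from the protocol:

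- Recruitment of 500 to 1000 patients a year (Sample size calculation).
- Recurrence: "This includes recurrent urolithiasis in 50% of patients within 5 years" (Background). Under a constant hazard the annual risk is 1 − 0.5^(1/5) = 0.129. Both 12.9% and 50% were used. Carrying this figure over to registry patients, who have already had at least two events, is an assumption.

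Assumed inputs:

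- Three independent, normally distributed known factors with a joint true c of 0.60, 0.65 or 0.70. With c = Φ(d/√2), the separation is d = √2·z(c), that is 0.358, 0.545 or 0.742.
- Five new factors that are pure noise.
- Single-level logistic models without imputation; 300 replicates per setting.

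The standard error of c is the Hanley–McNeil form, SE² = [c(1−c) + (n₁−1)(q₁−c²) + (n₀−1)(q₂−c²)]/(n₁n₀), with q₁ = c/(2−c) and q₂ = 2c²/(1+c). New-data c was computed in 20,000 independent patients. The nested test is a likelihood-ratio test on 5 degrees of freedom at the 5% level.

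| n | Recurrence | True c, known | Apparent c: known / full | Full-model 95% CI above 0.5 | New-data c: known / full | Nested test rejects |
|---|---|---|---|---|---|---|
| 500 | 12.9% | 0.60 | 0.612 / 0.640 | 97.7% | 0.583 / 0.566 | 4.3% |
| 500 | 12.9% | 0.65 | 0.658 / 0.679 | 100% | 0.641 / 0.624 | 5.0% |
| 500 | 12.9% | 0.70 | 0.703 / 0.718 | 100% | 0.694 / 0.680 | 4.3% |
| 500 | 50% | 0.60 | 0.607 / 0.621 | 100% | 0.593 / 0.582 | 4.0% |
| 500 | 50% | 0.65 | 0.654 / 0.664 | 100% | 0.646 / 0.637 | 5.7% |
| 500 | 50% | 0.70 | 0.703 / 0.710 | 100% | 0.697 / 0.690 | 5.7% |
| 1000 | 12.9% | 0.60 | 0.606 / 0.621 | 99.7% | 0.593 / 0.581 | 4.3% |
| 1000 | 12.9% | 0.65 | 0.653 / 0.664 | 100% | 0.646 / 0.636 | 5.3% |
| 1000 | 12.9% | 0.70 | 0.700 / 0.708 | 100% | 0.697 / 0.690 | 5.0% |
| 1000 | 50% | 0.60 | 0.603 / 0.610 | 100% | 0.597 / 0.590 | 8.7% |
| 1000 | 50% | 0.65 | 0.651 / 0.656 | 100% | 0.648 / 0.643 | 4.0% |
| 1000 | 50% | 0.70 | 0.700 / 0.704 | 100% | 0.698 / 0.695 | 4.7% |

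One case by hand: n = 1000, 12.9% recurrence, so n₁ = 129 and n₀ = 871, with full-model c = 0.664. Then q₁ = 0.497, q₂ = 0.530, SE = 0.0275, and the interval is 0.664 ± 0.054 = 0.610 to 0.718. It lies well above 0.5, although the five new factors are useless.

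Three readings follow.

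- In new data the full-model c is still 0.57 to 0.70. An interval of registry size would exclude 0.5 in 96 to 100% of replicates in eleven settings and in 34% in the other (n = 500, 12.9% recurrence, true c 0.60).
- The nested test rejects in 4.0 to 8.7%, on average 5.1%, as it should when nothing is added.
- The apparent gain in c from useless factors is positive (0.004 to 0.028), whereas the gain in new data is slightly negative (−0.003 to −0.017). The gain itself therefore needs optimism correction.

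**The case against.** The other side has five good arguments.

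- *The analysis plan may cover it.* A plan is promised, the protocol speaks of regression models in the plural, and calculating a c statistic does not rule out reporting its change. This stands as a limit: the point is not that a nested comparison has been rejected. But the article does name a measure of predictive power, and that measure does not answer the incremental part of its question.
- *No 0.5 benchmark is stated.* A reader might infer that any c above 0.5 will be declared a success and credited to the lifestyle items. The protocol sets no test, threshold or success criterion, so that inference is not supported. The simulated c above 0.5 is also close to built in, since the known factors were given real predictive strength.
- *The regression adjusts.* If known and new factors enter the logistic or Cox model together, adjusted coefficients show independent association, and a joint test of the new ones would come close to what is asked for. So it would be wrong to say that the plan cannot separate old from new at all. What remains is that the article does not say known factors are included throughout, and that an adjusted association is not a gain in prediction.
- *The c statistic suits a risk score.* This is right. Developing and validating a score is part of the same research question, and overall discrimination is an apt description of it.
- *Single-factor ROC curves.* A reader might also infer that each new factor will be judged by its own ROC curve, where a mere proxy for known factors could look predictive. The protocol does not say so; its ROC analysis follows a multiple regression. The point does not rest on that reading.

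**Conclusion.** The point holds in limited form. One part of research question 2 is incremental, while the predictive measures fixed for it are overall measures on a mixed predictor set. Neither planned validation step isolates added value.

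The contrast between 98 to 100% and 4 to 9% illustrates how little the overall c says about the new factors. It does not estimate how often RECUR would mislead. It rests on the assumed known-factor strength, noise-only new factors and a constant hazard, and it ignores clustering and imputation. The mismatch between question and measure depends on none of these.

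The rest of the analysis for research question 2 is unaffected. This should be settled before the analyses are run, but it does not undermine the registry's design.

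**What to change.** For the incremental part of research question 2:

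1. List which factors from the Risk factors section the registry actually records, and which lifestyle and sociodemographic items count as new. The Outcomes section names stone composition and co-morbidity but not family history, early onset or anatomical abnormalities. Its list is open-ended, and the data catalogues are not shown. Any gain is relative to the known factors that are recorded.
2. Fit a two-level logistic reference model with those known factors, then add the new factors in the same patients and the same imputed data sets.
3. Report the joint test of the added factors, pooled over imputations, and the optimism-corrected gain in c statistic with its confidence interval, using the bootstrap already planned.
4. Repeat the comparison of the two models in the year-2 data.
5. Keep the overall c statistic and Youden Index as the description of the risk score.

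The cost is one extra model fit and a few sentences in the analysis plan. If step 1 is confined to recorded factors, no new data are needed. The reported gain will be smaller than the overall c statistic and will look less impressive.

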### Machine learning

In order to identify patient subgroups and treatment patterns, we will apply machine learning techniques, in particular variational auroencoders (VAEs) as a deep learning technique. This will allow us to cluster patients in an unsupervised manner, also taking time structure into account. This will be complemented by more standard descriptive statistics for comprehensively describing the characteristics of different patient subgroups, the disease course, and treatment paths. In years 1 and 2, this approach will primarily be used for quality control, whereby identified patterns will reveal artefacts in the data that need to be resolved, and help us prioritize measured patient characteristics for quality improvement. In year 5, the techniques will be deployed on a final analysis data set for identifying prognostically relevant patient subgroups, while also guiding propensity score development for the causal analyses described above. All analyses will be pre-specified in a statistical analysis plan.

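### The risk score is meant to predict a probability, but the only performance measures named assess discrimination and cannot show that predicted risks are too high, or by how much

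*Protocol article*

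**What the plan says.** All of this is in the protocol article.

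- **Background, Objectives (research question 2):** the registry is to develop a risk score for the probability of stone recurrence, validate it on longitudinal registry data, and draw implications for prevention and treatment.
- **Methods, Data analysis, model:** "Two-level multiple logistic regression models with the dependent variable stone recurrence will be conducted to account for cluster effects".
- **Same section, performance:** "By using Receiver Operating Characteristics (ROC) analyses, we will determine the predictive power of the risk factors". The next sentence adds: "The Youden Index and area under the curve (c statistic) will be calculated".
- **Same section, censoring:** because ROC curves ignore time to event and right censoring, "we will complement this analysis via survival analysis techniques like Kaplan–Meier or Cox regression analyses".
- **Same section, validation:** models from multivariable regression "lead to overestimated predictions when applied in new patients, we will internally validate our model with bootstrapping techniques". External validation is to be done by "comparing the prognostic capacity in the data set acquired in the first year with that in the second year".
- **Methods, Machine learning:** "All analyses will be pre-specified in a statistical analysis plan". That plan is not available here.

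The article nowhere mentions calibration, a comparison of predicted with observed risk, or a Brier score.

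**The concern.** A score that outputs a probability has to meet two separate requirements. It must rank patients correctly (discrimination), and the stated risks must agree with observed frequencies (calibration). The article names an aim that needs both and a hazard that, on its plain wording, concerns the second. The measures it then names address only the first.

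If validation were carried out with the named measures alone, a score with similar c statistics in both years could be called validated although its absolute risks were systematically too high. Any implication for prevention that depends on the level of risk, rather than on the order of patients, would inherit that error.

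**Working it through.** The article states no c statistic, event rate, predictor count or calibration figure, so there is no figure of its own to reproduce. The check concerns a property of the named measures. It was done by reasoning and then by simulation. **All event rates, predictor counts and effect sizes below are assumptions.** The only input from the article is the expected recruitment of 500 to 1000 patients per year (Sample size calculation); its lower end sets the sample size in step 4.

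**1. Why the measures do not respond.** The c statistic is the probability that a patient with recurrence has a higher predicted risk than one without (ties count one half). The maximum Youden Index is J = max over cut-offs of (sensitivity + specificity − 1). Both depend only on the order of the predictions, so any strictly increasing change to all predicted risks leaves them unchanged.

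**2. Predicted odds doubled** (logit + log 2; 400,000 simulated patients; linear predictor with SD 1). O/E is observed divided by mean predicted risk, computed before rounding.

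| True risk | Mean predicted, odds doubled | Observed | O/E | c, calibrated and doubled | Max. J, calibrated and doubled |
|---|---|---|---|---|---|
| 10% | 0.171 | 0.100 | 0.58 | 0.7469 | 0.3620 |
| 20% | 0.311 | 0.200 | 0.64 | 0.7438 | 0.3578 |
| 30% | 0.433 | 0.301 | 0.70 | 0.7430 | 0.3572 |
| 50% | 0.640 | 0.500 | 0.78 | 0.7394 | 0.3495 |

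Stretching the linear predictor by 1.5 (a calibration slope of 1/1.5 = 0.67) also leaves c and J unchanged. At 50% true risk its O/E is 1.00, so O/E alone would miss that error and the slope is needed as well.

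**3. A year-1 model carried into year 2.** The maximum Youden Index ignores a monotone change, but J at a fixed numerical cut-off need not. The year-1 cut-off was therefore kept while baseline risk fell. Mean predicted risk is 0.300 throughout; year-1 J is 0.3558.

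| Year-2 observed | O/E | c | J at year-1 cut-off |
|---|---|---|---|
| 0.300 (no change) | 1.00 | 0.7404 | 0.3507 |
| 0.232 | 0.232/0.300 = 0.77 | 0.7439 | 0.3550 |
| 0.192 | 0.192/0.300 = 0.64 | 0.7446 | 0.3545 |
| 0.142 | 0.142/0.300 = 0.47 | 0.7473 | 0.3535 |

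Even with predicted risk about twice the observed risk, neither measure gives a signal.

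**4. Overfitting.** Assumed: 500 patients, 25 predictors, 15.6% events (about 78 events, 78/25 ≈ 3 per predictor), 60 replicates, each applied to 20,000 new patients. The c statistic falls from 0.773 (apparent) to 0.672 (new patients), so a loss is visible. The calibration slope is 0.55, and in the top risk decile mean predicted risk is 0.49 against 0.34 observed. The drop in c does not convey that gap.

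**The case against.** **The analysis plan may add calibration.** The article says that all analyses will be pre-specified there, and an article may leave such detail to it. This would settle the matter if the article were merely silent on performance. It is not: it states the aim, the hazard and the measures, and these do not fit together. The analysis plan remains a suitable place for the correction.

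**The measures are not tied to validation.** The ROC sentences concern the predictive power of risk factors, while the validation paragraph speaks of prognostic capacity without attaching a measure. This is correct. A reader might infer that overestimated risks are bound to pass validation, but the text does not say that validation is confined to the c statistic. What stands is that no named measure would reveal the error.

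**Overestimated predictions may mean optimistic performance.** On that reading a bootstrap-corrected c is a matching remedy. The aim of predicting a probability would still lack a measure.

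**Overfitting does leave a trace.** Step 4 confirms this, so it would be wrong to say that the problem goes wholly unseen. Moreover, a logistic model with an intercept essentially reproduces the mean risk in its own development data. A uniform shift as in step 2 therefore arises from a changed baseline risk, as in step 3, rather than from overfitting.

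**Three further inferences are tempting but unsupported:**
- That shrinkage is ruled out. The article does not say how the bootstrap output will be used.
- That c is inflated by centre intercepts. Nothing says they enter it. Any inflation would depend on an assumed between-centre spread; with an SD of 0.3 on the logit scale it was only 0.67 against 0.66. The Discussion speaks of adding hospitals to the registry, not of applying the score there.
- That patients will be told wrong risks. The section on the patient app describes discussing a risk profile based on clinical findings and PROMs, not a probability from the score.

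**Conclusion.** The point holds in a limited form. The article aims at a predicted probability and expects overestimated predictions, but every performance measure it names assesses discrimination. Such measures can show some loss from overfitting. They cannot show that the level of predicted risk is too high, or by how much.

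The insensitivity of c and of the maximum Youden Index to a monotone change in predicted risk is a mathematical property and needs no assumption. The sizes are illustrations under assumed inputs: with odds doubled, O/E runs from 0.58 to 0.78 over true risks of 10% to 50%. They do not forecast miscalibration in RECUR.

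This should be fixed but is not critical. No data would be lost, and the risk-factor analyses are to be repeated annually, so calibration can be added at any cycle.

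**What to change.** In Data analysis (or the analysis plan), name calibration as a performance measure beside the c statistic:

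- observed/expected ratio or calibration-in-the-large, calibration slope, and a calibration plot;
- optimism-corrected in the bootstrap that is already planned;
- reported when the year-1 model is applied, unchanged, to the year-2 data.

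This takes one or two sentences and a little programming, with no new data. The downside is slightly more analysis work and possibly less favourable reported performance. Shrinkage or penalised estimation, and computing performance within centres before pooling, are options for the analysis plan and not part of the required change.
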